### Sample size

Based on the study objectives, recruitment feasibility, and the desired precision of estimates (i.e., two-sided 95% confidence intervals [CIs]), the sample size was calculated using PASS Sample Size software. Antibiotic use will be compared between both Arm 2 and Arm 3 versus Arm 1 (*N* = 1500) at the first consultation and will serve as a secondary outcome. The effect of the educational measures on the use of OTC antibiotics will be compared between Arm 2 and Arm 3 (*n* = 1000) at 4 weeks and 4 months of follow-up.

It is estimated that approximately 85% of women in LLMICs are over-treated with antibiotics for VD, and around 50% receive antibiotics that contribute to AMR. Furthermore, about 40% of women are expected to purchase antibiotics OTC. The overtreatment with antibiotics and the use of AMR will be assessed at the first consultation whilst the adherence to the treatment recommendation will be assessed at 4 weeks as primary outcome and at 4 weeks and 4 months of follow-up as secondary outcome.

With 1500 participants randomized equally across the three arms (allocation ratio of 1:1:1), a 10–20 percentage point difference between groups in any of these measures will produce CIs with a width of 8–12%, achieving at least 90% power for each comparison at a significance level of 0.017 (adjusted from 0.05 to account for multiplicity with three primary outcome measures). For the assessment of over-the-counter antibiotic use, even with a 40% loss to follow-up, the expected CI width remains around 15%.

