#### Primary outcome analyses

Two of the three primary endpoints (a) the proportion of participants overtreated with antibiotics and (b) the proportion of participants being prescribed AMR-driving antibiotics will be compared between groups (Arm 1 *vs* Arm 2 + 3). The third primary endpoint, (c) the proportion adhering to treatment recommendations at 1 month follow-up, will be compared between groups Arms 2 vs 3. The risk difference and corresponding 95% confidence intervals, as well as p-values calculated from chi-squared tests, will be reported. *P*-values below 0.017 will be regarded as statistically significant due to there being three primary outcomes.

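### The fixed 0.017 threshold for all three primary outcomes is valid, but it gives up power on adherence that Holm's procedure would recover when the prescribing outcomes succeed

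*Protocol article*

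**What the plan says.** Primary outcome analyses names three primary endpoints. Overtreatment (a) and AMR-driving prescriptions (b) compare Arm 1 with Arms 2 and 3 combined. Adherence at one month (c) compares Arm 2 with Arm 3. On reporting, the section says: "The risk difference and corresponding 95% confidence intervals, as well as p-values calculated from chi-squared tests, will be reported". On the decision, p-values "below 0.017 will be regarded as statistically significant due to there being three primary outcomes".

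Sample size uses the same threshold, described as "adjusted from 0.05 to account for multiplicity with three primary outcome measures". It bases precision on "two-sided 95% confidence intervals [CIs" and states that "a 10–20 percentage point difference between groups in any of these measures will produce CIs with a width of 8–12" per cent, "achieving at least 90% power for each comparison". The article gives no ordering or step-down rule and no adjusted interval level.

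**The concern.** Each outcome faces 0.017 whatever happens to the other two. Outcomes (a) and (b) compare 500 women with 1000 and are recorded at the first consultation. Outcome (c) compares 500 with 500 and is known only for women reached by telephone. It is also the primary outcome that tests what Arm 3 adds to Arm 2. Under Holm, once (a) and (b) are rejected, (c) is tested at 0.05.

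Recruitment has closed at 1500 (Trial status), so power for (c) can no longer be raised by enrolling more women. The testing rule can still be improved.

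A lesser reporting point goes with it. An outcome with p between 0.017 and 0.05 would appear with a 95% interval that excludes zero and a verdict of not significant. The article does not say that the interval is unadjusted.

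**Working it through.** **Inputs from the article.** 1500 women allocated 1:1:1; base rates of 85% overtreated, 50% given AMR-driving antibiotics and 40% buying antibiotics over the counter; differences of 10–20 points; 40% loss considered for over-the-counter use (Sample size); 20% missingness as the trigger for considering imputation (Protocol non-adherence and missing data).

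**Assumption.** No adherence rate is given. I take 40% v 30% non-adherent (the same as 60% v 70% adherent) from the over-the-counter figure, and show 50% v 60% and 70% v 80% as a range.

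**Formula.** Two-sided chi-squared power ≈ Φ[(δ − z·SE₀)/SE₁], with SE₀ pooled and SE₁ unpooled. z = 2.387 at 0.017, 2.394 at 0.05/3, 2.241 at 0.025 and 1.960 at 0.05.

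**The plan's own figure (at least 90% at 0.017, 10 points).**
- (a) 85% v 75%, 500 v 1000: (0.1 − 2.387×0.02256)/0.02104 = 2.19, power 98.6%.
- (b) 50% v 40%, 500 v 1000: (0.1 − 2.387×0.02714)/0.02720 = 1.29, power 90.2%.
- (c) 40% v 30%, 500 v 500: (0.1 − 2.387×0.03017)/0.03000 = 0.93, power 82.5%.

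The stated power reproduces for (a) and (b). For (c) it depends on the assumed rate: 78.7% for 50% v 60%, and about 90% for 70% v 80%.

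**Power for (c) under Holm.** Let C₁, C₂, C₃ be the power for (c) at 0.05/3, 0.025 and 0.05. Let U be the probability that at least one of (a), (b) has p ≤ 0.05/3. Let V be the probability that the smaller of their p-values is ≤ 0.05/3 and the larger ≤ 0.025. With (c) independent of (a) and (b):

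Power = C₁ + (C₂ − C₁)·U + (C₃ − C₂)·V

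With 10-point effects, (a) has power 0.9856 at 0.05/3 and 0.9906 at 0.025; (b) has 0.9010 and 0.9250. Taking (a) and (b) as independent:
- U = 1 − 0.0144×0.0990 = 0.9986.
- V = 0.9906×0.9250 − 0.0050×0.0240 = 0.9162.
- 40% v 30%, 500 per arm: 0.8228 + 0.0370×0.9986 + 0.0537×0.9162 = 0.909.

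| Outcome (c) | Per arm | Fixed 0.017 | Holm |
|---|---|---|---|
| 40% v 30% | 500 | 82.5% | 90.9% |
| 40% v 30% | 400 (20% loss) | 72.0% | 83.7% |
| 40% v 30% | 300 (40% loss) | 57.2% | 72.1% |
| 50% v 60% | 500 | 78.7% | 88.4% |
| 50% v 60% | 300 | 53.0% | 68.4% |
| 70% v 80% | 500 | 89.9% | 95.3% |
| 70% v 80% | 300 | 67.2% | 80.2% |

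Simulation agrees to within about a point, and a correlation of 0.5 between (a) and (b) still gives about 91% in the first row.

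**When the gain shrinks (40% v 30%, 500 per arm).** If only (a) has an effect, power goes from 82.5% to 86.1%. If neither (a) nor (b) has one, it stays at about 82.4%. For 40% v 20%, power is about 100% under either rule.

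**Intervals.** The planned widths are 95% widths: 8.3 points for (a), 10.7 for (b), 11.8–12.3 for (c), and 15.2 for 40% v 30% with 40% loss. At 98.3% they would be 10.0–10.1, 13.0, 14.4–15.0 and 18.5.

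For (c) at 40% v 30%, p falls between 0.017 and 0.05 in 91.3 − 82.5 ≈ 9% of trials at 500 per arm and 72.9 − 57.2 ≈ 16% at 300. These are the trials in which the current rule and the 95% interval disagree. Pairing Holm with 98.3% intervals would reverse the conflict, not end it. Holm would reject while the interval included zero in 90.9 − 82.3 ≈ 8.6% of trials at 500 per arm and 72.1 − 56.9 ≈ 15% at 300.

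**The case against.** The article commits no statistical error here. Bonferroni is prespecified, both sections use the same 0.017, and familywise error is held apart from rounding (3 × 0.017 = 0.051). A reader might infer that the significance rule is invalid or that the two sections conflict; neither is so. Bonferroni also has exact matching simultaneous intervals, a fair reason to prefer it in a trial that reports risk differences, and Holm has no simple counterpart. That stands as a real cost of switching.

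The gain is also conditional. It needs at least one prescribing outcome to be rejected, and it is largest at the low end of the 10–20 point range with mid-range adherence rates that the article does not give. Adherence is defined by three conditions (Outcomes), so the over-the-counter figure is only a proxy. A reader might infer that Holm always recovers the lost power, or always restores 90%; the figures support neither. The shortfall against the stated 90% is a separate sample-size matter and does not make the testing rule wrong.

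Timing carries weight too. Version 6 is dated after recruitment closed, so first-consultation prescriptions were already recorded. A change to a more liberal rule is credible only if made, dated and justified before anyone sees results by arm. Because the article says the statistician is blinded and follow-up was due to run to December 31, 2025, this objection sets a condition; it does not defeat the change.

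Finally, the p-value already decides, so no verdict is ambiguous under the present text. The interval point is one of labelling.

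**Conclusion.** The concern holds as one of efficiency, not validity. The fixed 0.017 rule controls error but costs adherence about 8 points of power at 500 per arm, 12 at 400 and 15 at 300, assuming 40% v 30% and 10-point effects on both prescribing outcomes. At 70% v 80% the cost is about 5 points at 500 per arm. It is about 4 points at 500 per arm (40% v 30%) if only overtreatment responds, and nil if neither prescribing outcome does or if the adherence effect is near 20 points.

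Holm at 0.05/3, 0.05/2 and 0.05 rejects everything that Bonferroni at 0.05/3 rejects, under any dependence between the outcomes. The only exception against the present text is a p-value in the sliver between 0.0167 and the rounded 0.017. The change is worth making because it falls on the most weakly powered primary outcome and needs no more participants.

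**What to change.** Before unblinded analysis, and with a dated amendment:

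- Replace the fixed threshold in Primary outcome analyses with Holm: order the three p-values, compare them in turn with 0.05/3, 0.05/2 and 0.05, and stop at the first failure.
- Report Holm-adjusted p-values and state that they alone decide significance.
- Label the 95% intervals as unadjusted and not decisive.
- Do not present 98.3% intervals as the matching interval, since they can contradict a Holm rejection with p between 0.017 and 0.05.

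The cost is two or three sentences and no new data. The price is the loss of a simple simultaneous interval that agrees with every verdict. If the sponsor values that agreement more than the power, Bonferroni with 98.3% intervals remains a valid choice, but the article should then say so.

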#### Secondary outcome analyses

The binary secondary outcomes will be analysed using the same strategy as for the primary outcomes. An overall comparison of symptoms of vaginal discharge will be performed by the chi square test using three ordinal categories (better, unchanged, or worse). The secondary outcome patient satisfaction is measured on a Likert scale, and an appropriate statistical strategy will be considered after a blinded review of the distribution of scores.

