**Methods:**

This study is a randomized controlled double-blind, superiority trial with follow-up assessments at 4 weeks and 4 months conducted in a Nepalese teaching hospital and its outreach centers. Participants are randomly assigned to one of three study arms: Arm 1 receives treatment, based on syndromic management; Arm 2 receives POCT-guided treatment using the *Cepheid GeneXpert®* (for *Ct* and *Ng*), pH and whiff tests (for BV and *Tv*), and the *OSOM®* test (for *Tv*); Arm 3 receives the same POCT-guided treatment as Arm 2, plus an educational intervention, and referral for psychosocial concerns. The primary outcome is the proportion of participants overtreated with antibiotics at the primary consultation, comparing Arm 1 versus Arms 2 and 3. Secondary outcomes include over-the-counter antibiotic acquisition, subsequent health-seeking behavior, and changes in VD symptom development over time.

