### Trial design

This study is a randomized, controlled, double-blinded superiority trial. Study participants are randomly allocated into three parallel arms in a 1:1:1 ratio. The trial arms are as follows: 1. Treatment as usual, 2. Treatment based on POCT results, and 3. Treatment based on POCT results combined with education about VD and antibiotics and addressing psychosocial vulnerabilities (see Fig. 1).

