#### Comparisons

The trial compares the accuracy of antibiotic prescriptions between the current /syndromic and POCT-guided treatment arms. It also evaluates whether the addition of educational and psychosocial support improves adherence to treatment recommendations, influences health-seeking behavior, and affects symptom resolution and patient satisfaction.

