### Statistical analysis

Descriptive analysis will be used for demographic characteristics, reproductive history, questions related to VD, clinical findings, working diagnosis by health practitioners, microbiological results, anxiety and depression scores, prevalence of DV, and prescription of medications (including antibiotics). At follow-up, we will describe symptom development, treatment adherence, and patient satisfaction for all participants after one and four months. Anxiety and depression scores will be assessed for the remaining participants at the four-month follow-up, after recruitment is completed, due to time constraints. The expected sample size is approximately 400 participants.

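### Symptoms are tested only by an overall three-category chi-square, with no effect estimate, confidence interval or named arm contrast, so a non-significant result would not show that less antibiotic use leaves symptoms unchanged

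*Protocol article*

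**What the plan says.** All places are in the protocol article.

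- **Secondary outcome analyses.** Binary secondary outcomes follow the primary strategy, which under Primary outcome analyses means a risk difference, a 95% confidence interval and a chi-squared p-value. Symptoms are handled separately: "An overall comparison of symptoms of vaginal discharge will be performed by the chi square test using three ordinal categories". The categories are better, unchanged and worse. The section does not say which arms are compared or at which follow-up.
- **Statistical analysis, opening paragraph.** Symptoms are also reported descriptively: "At follow-up, we will describe symptom development, treatment adherence, and patient satisfaction for all participants after one and four months".
- **Abstract, Methods.** The symptom outcome is secondary and is worded as "changes in VD symptom development over time".
- **Trial design.** "This study is a randomized, controlled, double-blinded superiority trial".
- **Comparisons.** Symptoms are linked to the add-on in Arm 3: "It also evaluates whether the addition of educational and psychosocial support improves adherence to treatment recommendations, influences health-seeking behavior, and affects symptom resolution". No section states an aim of showing that symptoms are no worse than under syndromic care.
- **Sample size.** "With 1500 participants randomized equally across the three arms (allocation ratio of 1:1:1"). No power, target difference or expected distribution is given for symptoms.

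**The concern.** The POCT strategy is meant to lower antibiotic use. None of the three primary outcomes (overtreatment, AMR-driving prescriptions, adherence) measures a cost of treating fewer women. Such a cost is conceivable on the article's own account. The section on protocol adaptation for *Tv* testing reports laboratory-confirmed *Tv* cases left untreated after negative POCT results, with 7.8% false negatives. The section on overview and rationale says that *Tv* and BV carry a high symptom burden. Symptom follow-up is the natural place to look.

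The analysis named for it is the least informative one in the section. A chi-square on three categories can be significant because women improved or because they got worse. When it is not significant, it does not say how large an excess of unimproved women remains compatible with the data. A reader of the results who asks what the prescribing change cost in symptoms would have raw percentages and a p-value. The point is the missing estimate and interval, not the test's neglect of category order.

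**Working it through.** **1. The plan's own precision figures, to confirm the method.** Wald width = 2 × 1.96 × √[p₁(1−p₁)/n₁ + p₂(1−p₂)/n₂].
- 85% vs 75%, 500 vs 1000: 8.2 points.
- 50% vs 40%, 500 vs 1000: 10.7 points.
- 40% vs 30%, 500 vs 500: 11.8 points; with 40% loss (300 vs 300), 15.2 points.

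These agree with the stated 8–12% and about 15%. For Arm 1 versus Arms 2+3 at 0.017, power is 98.6% for 85% vs 75% and 90.2% for 50% vs 40%. That fits the claim of "achieving at least 90% power for each comparison at a significance level of 0.017" for this contrast. None of these figures concerns symptoms.

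**2. Inputs for symptoms.** From the article: 500 women per arm, hence 500 vs 1000 for Arm 1 versus Arms 2+3, and 40% loss as the worst case (given there for over-the-counter antibiotic use, borrowed here). Assumed: the symptom distributions, an intermediate 20% loss, and a two-sided 0.05 level.

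**3. Power of the three-category test (2 df).** With p̄ₖ = (n₁p₁ₖ + n₂p₂ₖ)/(n₁+n₂),

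λ = [n₁n₂/(n₁+n₂)] × Σ (p₁ₖ − p₂ₖ)²/p̄ₖ, and power = P(χ²₂(λ) > 5.991).

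Worked case, 70/20/10 (Arm 1) to 65/22/13 (Arms 2+3): p̄ = 0.6667, 0.2133, 0.1200. The sum is 0.0025/0.6667 + 0.0004/0.2133 + 0.0009/0.1200 = 0.00375 + 0.00188 + 0.00750 = 0.01313. Then λ = 333.3 × 0.01313 = 4.375, and power is 45%. Loss scales λ to 3.50 (20%) and 2.625 (40%), giving 37% and 29%.

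Each row has a 5-point fall in *better*:

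| Better/unchanged/worse, Arm 1 → Arms 2+3 | λ, no loss | Power at 0 / 20 / 40% loss |
|---|---|---|
| 60/30/10 → 55/35/10 | 3.97 | 41 / 34 / 26% |
| 70/20/10 → 65/22/13 | 4.38 | 45 / 37 / 29% |
| 60/25/15 → 55/25/20 | 6.02 | 59 / 49 / 38% |
| 70/20/10 → 65/20/15 | 7.50 | 69 / 58 / 46% |
| 80/15/5 → 75/15/10 | 11.09 | 86 / 76 / 63% |

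The range is 26% to 86% for these rows and is not a bound. If worsening is rarer still (85/12/3 → 80/12/8), power is 93 / 86 / 75%. If the 0.017 level carried over, the second row would fall to 29 / 22 / 16%.

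**4. What an interval would give.** Half-width = 1.96 × √[p(1−p)(1/n₁ + 1/n₂)], assuming p = 0.30 *not better* in both groups.
- Arms 2+3 vs Arm 1, no loss: 1.96 × √(0.21 × 0.003) = 1.96 × 0.0251 = 4.9 points.
- Same contrast, 40% loss (300 vs 600): 1.96 × 0.0324 = 6.4 points.
- Arm 3 vs Arm 2: 5.7 points with no loss (500 vs 500) and 7.3 points with 40% loss (300 vs 300).

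If the observed difference were zero, the interval would thus rule out an excess beyond about 5 to 6.5 points for Arms 2+3 versus Arm 1. The chi-square reports no such limit.

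**The case against.** The strongest reply is that the plan is being held to an aim it does not state. It declares superiority, ties symptom resolution to the education and psychosocial add-on (Arm 3 versus Arm 2), and a difference test suits that question. This stands as far as it goes: no aim of showing symptoms to be no worse is written, and the Arm 1 contrast for symptoms is one that a reader would bring. It does not supply the missing estimate, which the add-on question needs as well.

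Three stronger readings are tempting, and the documents do not support them.
- *That the test would miss a 5-point worsening more than half the time.* This depends on the assumed distribution. It is true in some rows above and false in others. Where *worse* itself rises from 10% to 15%, power stays above half until loss approaches 40%.
- *That non-significance will be passed off as absence of harm.* The article says nothing of the kind.
- *That a non-inferiority margin is required.* In a declared superiority trial this is a trade-off. With 30% *not better* in both groups, the chance that the interval excludes a true margin is 51 / 43 / 34% for 5 points (0 / 20 / 40% loss), 85 / 76 / 64% for 7.5 points and 98 / 95 / 87% for 10 points. A margin looks comfortable only when it is wider than 5 points.

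It is also fair that symptoms are described at one and four months, so the chi-square is the only inferential analysis rather than the only one. Missed *Ct*, *Ng* and *Tv* cases are offered treatment later, which narrows one route to harm. Finally, detail on secondary outcomes is often left to an analysis plan. Here, however, the article does fix a method for symptoms, and it is less informative than the one it fixes for binary outcomes in the same section.

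**Conclusion.** The point holds as a modest, inexpensive improvement. Symptoms receive an overall chi-square with no effect estimate, interval or named contrast, while binary secondary outcomes receive a risk difference with a 95% interval. Under the five assumed distributions (5-point fall in *better*, 500 vs 1000 women, 0.05, up to 40% loss) power is about 26% to 86%. A non-significant result would therefore not show that less antibiotic use leaves symptoms unchanged.

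The power range rests on assumed distributions and on a loss figure that the article gives for another outcome. The absence of an estimate and interval rests on the text alone. An interval does not create precision that the sample lacks, but it reports the precision there is.

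**What to change.** Add to Secondary outcome analyses, before unblinding:

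- At 4 weeks, the risk difference in *not better* (unchanged or worse) with a 95% confidence interval, for Arms 2+3 versus Arm 1 and for Arm 3 versus Arm 2.
- The upper limit of the interval is reported as the largest excess not excluded.
- A non-significant chi-square is not reported as equivalence or as absence of a symptomatic cost.

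The chi-square can stay. The data come from the telephone follow-up already planned and the format is the one already used for binary outcomes, so the cost is a few lines of text and one more secondary estimate per contrast. If the sponsor wants to make a formal claim that symptoms are no worse, it would also have to fix a margin before unblinding; that is optional.

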#### Subgroup analysis

All primary and secondary outcomes will be analyzed based on two subgroup classifications: site (referral hospital and ORCs) and *Tv* test (before and after the introduction of an additional *Tv* test). Additionally, for the secondary outcome comparing the proportion of women acquiring OTC antibiotics after POCT-guided treatment (Arm 2 vs 3), this comparison will be analyzed in the subgroup of participants who screened positive for anxiety and depression and for those screening positive for DV.

The primary and secondary analyses are planned with an intention-to-treat approach, analyzing participants according to their allocated group regardless of treatment received or protocol deviations. A per protocol analysis will be considered depending on the proportion of non-adherence to the study protocol. We will describe the number and characteristics of non-eligible, non-included, and lost-to-follow-up participants. We will also describe the number and characteristics of non-eligible, non-included, and lost-to-follow-up participants.

### Protocol non-adherence and missing data

Protocol non-adherence is defined as participants in the intervention arms (arms 2 and 3) receiving antibiotics to treat *Ct*, *Ng*, *Tv,* or BV despite negative POCT results. These cases will be described in groups according to the three antibiotic treatment categories used: (a) treatment for *Ct*, (b) treatment for *Ng,* and (c) treatment for *Tv* and BV.

The proportion of missing data will be reported, and efforts will be made to determine the reason for missingness. The primary analyses will be complete case analyses. Two of the primary endpoints are registered immediately after the intervention and will not be subject to any substantial missingness. The third primary outcome is recorded at 4 weeks post-intervention and may have a greater risk of missingness. Multiple imputation methods will be considered if this missingness exceeds 20%.

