#### POCT methods

aFor *Ct* and *Ng*, self-collected urine samples are analyzed using the *Cepheid GeneXpert®* molecular test, administered by RAs. Results are reported as positive or negative for *Ct* and/or *Ng* and shared with the attending health practitioner. The test is validated and demonstrates high sensitivity and specificity [22].bFor the initial diagnostic approach to *Tv* and BV, each participant self-collects a vaginal discharge sample using a swab. The RA then measures the pH of the sample; if the pH is above 4.5, a drop of potassium hydroxide (KOH) is added to perform the whiff test, where a fishy odor indicates a positive result [23]. The health practitioner is subsequently informed of the pH level (above or below 4.5) and whether the whiff test result is positive or negative.cFor the diagnostic approach after protocol adaptation (see 2.5.4); for VD with pH > 4.5 and a negative whiff test, an antigen-based Tv test (*OSOM®*) is applied. Results from this test (positive/negative) are shared with the health practitioner.

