### Outcomes

The primary outcome measures are:The proportion of participants overtreated with antibiotics at the primary consultation with the health practitioner Overtreatment is defined as receiving a cephalosporin and/or macrolide when *Ng* is negative; a tetracycline or macrolide when *Ct* is negative; or a nitroimidazole when the gold standard test for *Tv* or BV is negative, (medications as specified in the Nepali STI case management guidelines) [15] (comparing arm 1 with the combined arms 2 and 3).The proportion of participants prescribed AMR driving antibiotics (Cephalosporins, Azithromycin, Ciprofloxacin) at the primary consultation with the health practitioner. comparing treatment as usual (arm 1) with POCT-based treatment (arms 2 and 3).The proportion of participants adhering to treatment recommendations, comparing arms 2 and 3. Adherence is assessed during telephone follow-ups after one month and is defined as follows: (a) participants report that they took the prescribed medication; (b) no additional purchase of antibiotics; and (c) no purchase of other medication for VD.

The study also examines six secondary outcome measures at various time points. The baseline data from this trial will also contribute to the analysis of the epidemiology of VD and infection including psychosocial factors, and measure the diagnostic accuracy of the POCT.

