#### Laboratory diagnostics

Gold standard STI testing includes the following: *Cepheid GeneXpert*® for *Ct*, *Ng,* and *Tv*. For BV, dried wet mounts from vaginal smears are collected for Nugent scoring and wet mount microscopy. All tests are performed by RAs, except Nugent scoring (performed by microbiologist [name]) and wet mount microscopy (performed by [name]). Nugent scoring is considered the gold standard for BV. For quality control, 10% of slides are double read by a second microbiologist ([name]).

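### A per-protocol set built on the article's only definition of non-adherence would select on primary outcomes 1 and 2, and in Arms 2 and 3 only

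*Protocol article*

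**What the plan says.** Under *Protocol non-adherence and missing data* the article gives its only definition: "Protocol non-adherence is defined as participants in the intervention arms (arms 2 and 3) receiving antibiotics to treat" Ct, Ng, Tv or BV although the POCT was negative. These cases are to be described by antibiotic category. Arm 1 has no counterpart; under *Trial arms* its prescribers do not see POCT results.

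The text under *Subgroup analysis* sets the analysis populations. The main rule is: "The primary and secondary analyses are planned with an intention-to-treat approach, analyzing participants according to their allocated group regardless of treatment received or protocol deviations". It then adds: "A per protocol analysis will be considered depending on the proportion of non-adherence to the study protocol". The article gives no threshold or direction for that decision and names neither the women to be excluded nor the outcomes concerned.

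Primary outcome 1, under *Outcomes*, is overtreatment at the primary consultation: "Overtreatment is defined as receiving a cephalosporin and/or macrolide when" Ng is negative, with a parallel clause for Ct. The Tv/BV clause reads "nitroimidazole when the gold standard test for" either condition is negative. Primary outcome 2 is: "The proportion of participants prescribed AMR driving antibiotics (Cephalosporins, Azithromycin, Ciprofloxacin) at the primary consultation with the health practitioner". Both compare Arm 1 with Arms 2 and 3 combined.

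**The concern.** Receiving an antibiotic despite a negative test is, to a large extent, what primary outcome 1 counts, and such prescriptions also feed outcome 2. If a per-protocol set removes women for this reason, it selects on the outcome after randomisation. It can do so only in Arms 2 and 3, because in Arm 1 there is no POCT result to act against.

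Prescribers treating despite a negative POCT is a main way in which the POCT strategy could fail. A set that leaves those consultations out hides that failure and cannot serve as a check on the intention-to-treat result. At stake is a supportive analysis that could show a large benefit where none exists, or exaggerate a real one.

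**Working it through.** **Inputs from the article.** Under *Sample size*: 1500 women allocated 1:1:1, so 500 in Arm 1 against 1000 in Arms 2+3; overtreatment about 85%; AMR-driving antibiotics about 50%; differences of 10–20 points; alpha 0.017; power at least 90%; confidence interval width 8–12%.

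**1. The plan's own figure.** Normal approximation, pooled variance under the null, critical value 2.387:
- 85% v 75%: SE = √(0.85×0.15/500 + 0.75×0.25/1000) = 0.0210; power 98.6%; 95% CI width 2×1.96×0.0210 = 8.2 points.
- 50% v 40%: SE = √(0.50×0.50/500 + 0.40×0.60/1000) = 0.0272; power 90.2%; width 10.7 points.

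The stated design reproduces for the comparisons at issue here.

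**2. How far the two definitions overlap.** For Ct and Ng, *POCT methods* says "self-collected urine samples are analyzed using the" Cepheid GeneXpert test, and the list in *Laboratory diagnostics* that begins "Gold standard STI testing includes the following" names the same platform. For Tv and BV the POCT is pH and whiff (later with OSOM), while the reference is GeneXpert for Tv and the Nugent score for BV. In Arms 2 and 3:

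| Prescription | Non-adherent | Overtreated |
|---|---|---|
| For Ct or Ng, both negative | yes | yes |
| Macrolide for Ct, woman Ct-positive and Ng-negative | no | yes, read literally |
| Nitroimidazole, POCT and reference both negative | yes | yes |
| Nitroimidazole, POCT false positive | no | yes |
| Nitroimidazole, POCT false negative | yes | no |

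The overlap is nearly complete for Ct/Ng and partial for Tv/BV.

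**3. Effect of exclusion on outcome 1.** Let p be the overtreatment rate in Arms 2+3 and s the share of overtreated women who count as non-adherent. Removing them, and nobody from Arm 1, gives a per-protocol rate of r = p(1−s)/(1−ps). This ignores the removal of correctly treated, POCT-negative women (last table row). With p = 85% in all arms (no true effect):

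| s (assumed) | r | Apparent difference |
|---|---|---|
| 50% | 0.425/0.575 = 73.9% | −11.1 points |
| 75% | 0.2125/0.3625 = 58.6% | −26.4 points |
| 90% | 0.085/0.235 = 36.2% | −48.8 points |
| 100% | 0/0.15 = 0% | −85.0 points |

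With a real 10-point effect (85% v 75%) and s = 50%, r = 0.375/0.625 = 60%, so 10 points become 25.

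**4. Outcome 2.** At 50% in all arms, if 90% of the AMR-driving prescriptions in Arms 2+3 were given against a negative POCT, the rate falls to 0.05/0.55 = 9.1%, an apparent 40.9-point reduction. The 90% is an assumption.

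**5. Which shares are plausible.** A simulation took the Ct/Ng POCT as equal to its reference and combined Tv/BV POCT accuracy as perfect, 87%/87%, or 51.8%/78.8% (sensitivity/specificity; the last two from figures in *Background*). The following are assumptions: Ct 4%, Ng 1%, Tv or BV 30%, syndromic prescribing of Ct/Ng drugs 50% (range 30–50%) and of nitroimidazole 80% (range 60–93%).
- POCT ignored (true null): s is 89–95% at the two imperfect accuracies and 100% with a perfect test. In the base case Arm 1 is at 78%, and the per-protocol rate in Arms 2+3 is 0%, 15% or 27%, a spurious reduction of 51–78 points (43–83 over the prescribing range).
- POCT followed in 80% of consultations: s is 45–66% at the imperfect accuracies. The intention-to-treat effect is then real, and the per-protocol set exaggerates it. In the base case at 87%/87%, 78% v 23% becomes 78% v 9% (55 points become 69). Over the prescribing range and both imperfect accuracies the exaggeration is 9–14 points.
- Between 2% and 10% of non-adherent women were not overtreated.

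**The case against.** The strongest reply is that the article never says these women will be excluded. The definition sits beside a plan to describe such cases, and the per-protocol analysis is only to be considered. Its population could be set in an analysis plan that is not shown. That stands as to certainty. It does not remove the point, because the article makes the per-protocol decision depend on the proportion of non-adherence and gives only this meaning for non-adherence.

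Four stronger readings are tempting, and the documents do not support them.

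- *Non-adherence simply is overtreatment, so the per-protocol rate in Arms 2 and 3 is zero by construction.* The table in step 2 shows otherwise. For Tv and BV the references differ, and *Protocol adaptation for Tv testing* reports more false negatives (7.8%) than correctly identified cases (3.7%) under the initial approach. Even for Ct/Ng, the macrolide clause read literally breaks the identity.
- *Outcome 2 would be emptied in the same way.* It counts listed drugs for any indication, and practitioners are free to give concomitant care. Only prescriptions for the four target conditions against a negative POCT would go. The article gives no figure for that share. Nor is its 50% rate a rate of Ct/Ng overtreatment, so a contrast of 50% with 0% on that component cannot be drawn from it.
- *The analysis is triggered when non-adherence is high, where the bias is worst.* That may be the intention, but no direction is stated.
- *The primary result is compromised.* Intention-to-treat is fixed as the approach for primary and secondary analyses.

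The one-sidedness argument also does not carry over to primary outcome 3. That outcome compares Arm 2 with Arm 3, and the definition covers both arms.

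**Conclusion.** The concern holds conditionally. If the stated definition is used to form a per-protocol set for Arm 1 versus Arms 2+3, that set largely conditions on primary outcome 1 and on those outcome 2 prescriptions given against a negative POCT, and it removes events from one side only.

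With no true effect at the article's 85%, the spurious reduction runs from about 11 to 85 points as the assumed share of overtreated women counted as non-adherent runs from 50% to 100%. The upper part of that range is the relevant one if prescribers ignore the POCT. Lower shares go with a POCT that is mostly followed, where the error is exaggeration of a real effect. Even the smallest figure is as large as the lower end of the 10–20 point difference in the sample size section.

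The result rests on the inferred exclusion, on the assumed shares, and on the same GeneXpert result serving as both POCT and reference for Ct/Ng. The intention-to-treat result, sample size and alpha are untouched, so the severity is moderate: a badly fixed rule for an optional analysis.

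**What to change.** State under *Protocol non-adherence and missing data* that the definition is for description only and will not define an analysis set for primary outcomes 1 and 2. The description by antibiotic category, already planned, should stay.

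If a per-protocol set is still wanted for those two outcomes, define it by process deviations that do not involve the prescription and are specified for every arm. Examples are an ineligible participant, the wrong arm delivered, the POCT not run or its result not delivered in Arms 2 and 3, and a POCT result disclosed in Arm 1.

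The cost is a wording change and one optional sensitivity analysis dropped or redefined; no data collection or sample size changes. Recruitment is complete and follow-up was due to end on 31 December 2025, so the wording should be settled before any unblinded analysis.
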